#### 4.5.4.3 Storage

---

Investigational product/placebo must be stored in a locked cabinet with limited access. The drug should be stored at the temperature between 20°-25°C (68°-77°F) protected from bright light. A temperature log shall be maintained at the study site.

#### *4.5.4.4 Study Drug Accountability*

---

Study drug shipment to sites will be accompanied by a Drug Shipment Form which must be signed and dated upon receipt and faxed back to the sponsor/CRO. This form must be filed in the Regulatory Binder. Drug accountability, per patient, will be performed by investigator staff at the Enrollment, Admission and 35-days visit.

The total study inventory by site and for the study as a whole will be reconciled at the end of the study. Any unused drug inventory will be processed for disposal or return.

Research pharmacist or the Site Coordinator, if Research Pharmacist is not available at the site, responsible for the study will detail the procedures for handling the Study Drug.

#### *4.5.4.5 Assessment of Patient Compliance*

---

Compliance will be recorded by the study research coordinator or investigator during the Admission and 35-days follow-up visits and must be documented on the appropriate source document (Medication Compliance section). Subjects must have 80% or greater compliance in each of the medication periods (14-17 days prior to surgery and 28 days after the surgery.)

- As an example, the subject is considered compliant in the period 14 days prior to surgery if he/she has taken at least 23 capsules.
- The subject is considered compliant in the 28 days medication treatment period after the surgery if he/she has taken at least 45 capsules.

Failure to comply will be considered a Protocol Violation and will be recorded on the Protocol Violation Log. Non-compliant subjects will remain in the study and will undergo the same study procedures as compliant subjects.

#### *4.5.5 Surgical Procedure*

---

The decompressive/reconstructive surgery for CSM will be performed per standard of care at the treating institution. The surgical approach, medical devices and bone grafts/bone graft substitutes used will be at the surgeon's discretion.

#### *4.5.6 Post-surgical Rehabilitation and Procedures*

---

Post-treatment procedures will be per the standard of care.

#### 4.5.7 Clinical Laboratory Procedures

**Table 2 Clinical lab blood tests**

| Examination                                                | Screening | Admission | 35 days $\pm$ 5 days |
|------------------------------------------------------------|-----------|-----------|----------------------|
| AST, SGOT                                                  | X         | X         | X                    |
| ALT, SGPT                                                  | X         | X         | X                    |
| Creatinine (mg/dL)                                         | X         | X         | X                    |
| Red Blood Cell (RBC) Count ( $\times 10^6/\mu\text{L}$ )   | X         | X         | X                    |
| White Blood Cell (WBC) Count ( $\times 10^6/\mu\text{L}$ ) | X         | X         | X                    |
| Hemoglobin or Hbg (gm/dL)                                  | X         | X         | X                    |
| Hematocrit or Hct (%)                                      | X         | X         | X                    |
| Polymorphonuclear Cells (%)                                | X         | X         | X                    |
| Immature Polys (%)                                         | X         | X         | X                    |
| Lymphocytes (%)                                            | X         | X         | X                    |
| Monocytes (%)                                              | X         | X         | X                    |
| Eosinophils (%)                                            | X         | X         | X                    |
| Basophils (%)                                              | X         | X         | X                    |
| Platelet Count ( $\times 10^3/\mu\text{L}$ )               | X         | X         | X                    |
| Mean Cell Hemoglobin Concentration (gm/dL)                 | X         | X         | X                    |
| Reticulocyte (%)                                           | X         | X         | X                    |

#### 4.6 Subjects Completion and Disposition

##### 4.6.1 Screen Failure

Screen failure is defined as a subject who has signed Informed Consent Form but does not meet the inclusion or exclusion criteria. A subject may be considered a screen failure any time prior to randomization. Screen failures will complete the screening source worksheet and the reason for failure will be provided.

##### 4.6.2 Enrolled Subject

A subject is considered to be enrolled when the randomization occurs.

##### 4.6.3 Withdrawn Subject

Reasonable efforts to keep each subject in the study will be made and must be documented by the investigator. A subject will be withdrawn from the study for any of the following reasons:

## Efficacy of Riluzole in Patients with Cervical Spondylotic Myelopathy Undergoing Surgical Treatment. A Randomized, Double-Blind, Placebo-Controlled, Multi-Center Study

- Subject voluntarily withdraws consent after the randomization and terminates participation. Such subject will not be replaced.
- The investigator withdraws the subject at any time for safety reasons or non-compliance with the study protocol or procedures. Such subject will not be replaced.

For each case, detailed information will be obtained explaining circumstances leading to the withdrawal. This will be recorded on the Subject Withdrawal Form and in the source document. Study drug assigned to the withdrawn subject shall not be assigned to another subject. The remaining study medication for the withdrawn subject will be returned from subject and/or kept at the site and processed at the end of the study according to the disposal or return instructions. For safety reasons, the subject who withdraws from the study for any reason before completion of the dose regimen and the last scheduled lab test will be provided for safety evaluation purpose. This shall occur within 30 days of the last dose of the Study Drug.

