### 5.10.1 Intention-to-Treat

---

Consenting patients who qualify and are randomized to a study arm (i.e. enrolled subjects) will be included in the Intent-To-Treat (ITT) analytic sample primary analysis population, regardless of the actual treatment received. Screen failures will be recorded on a screening eCRF and will not be included in the ITT group. Values for the patients who do not have the 6-month end point will be imputed to create complete ITT population.

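### Sections 4.5.4.5 and 4.6.3 disagree on whether medication-non-compliant subjects stay in the study, and 4.6.3 does not separate stopping study drug from ending follow-up, so observable 180-day mJOA scores may be lost and imputed

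*Protocol*

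**What the plan says.** Section 4.5.4.5 sets the medication standard: "Subjects must have 80% or greater compliance in each of the medication periods". It then says "Failure to comply will be considered a Protocol Violation and will be recorded on the Protocol Violation Log", and immediately adds "Non-compliant subjects will remain in the study and will undergo the same study procedures as compliant subjects".

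Section 4.6.3 opens with a retention duty, "Reasonable efforts to keep each subject in the study will be made and must be documented by the investigator", followed by "A subject will be withdrawn from the study for any of the following reasons". One reason is withdrawal of consent. The other is "The investigator withdraws the subject at any time for safety reasons or non-compliance with the study protocol or procedures". For a subject who leaves before finishing the dose regimen and the last scheduled laboratory test, the section describes a safety evaluation: "This shall occur within 30 days of the last dose of the Study Drug". It describes no efficacy assessment after withdrawal.

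Section 5.10.1 defines the ITT population by randomization, whatever treatment was received, and adds "Values for the patients who do not have the 6-month end point will be imputed to create complete ITT population". Section 5.10.5 makes ITT the primary efficacy population.

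**The concern.** Two things look wrong, and they are different in kind.

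The first is a contradiction. Section 4.5.4.5 calls medication non-compliance a protocol violation, so it falls within the non-compliance ground of section 4.6.3. Sites reading different sections could treat the same subject in opposite ways.

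The second is a gap. Apart from the sentence in 4.5.4.5, the protocol has no status for a subject who is off study drug but still followed. A subject withdrawn by the investigator on safety grounds has no stated route to a 180-day mJOA, even if willing to attend. Dosing ends 28 days after surgery and the primary endpoint is at 180 days, so stopping capsules does not in itself prevent that visit.

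What is at stake is the primary comparison. The affected subjects are selected after randomization, by safety or compliance. Section 6.1 lists twelve events seen more often on riluzole than on placebo, so unequal withdrawal between arms is plausible. A later analysis plan can choose an imputation method, but it cannot recover visits that were never made.

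**Working it through.** **Step 1: the two rules applied to one subject.** The pre-surgery period has 14 days × 2 = 28 capsules, and 80% of 28 is 22.4, which matches the 23-capsule threshold in 4.5.4.5. Take a subject who took 22 of 28 (78.6%).
- Under 4.5.4.5: a protocol violation, who stays and has every procedure.
- Under 4.6.3: non-compliant with the protocol, so the investigator may withdraw the subject from the study.

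Neither section refers to the other.

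**Step 2: whether withdrawal loses the endpoint.** Section 3.3 treats an active subject as one who is not withdrawn. Section 4.6.5 names withdrawal as a cause of missed visits. Section 4.5.1 requires clinic visits and rules out telephone or mail collection. Section 4.6.3 describes only the safety evaluation. No sentence forbids a 180-day mJOA after withdrawal, and none provides for one. Loss is what the text implies, not what it orders.

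**Step 3: reproduce the plan's operating characteristics.** Inputs: difference 0.9, SD 2.57, N = 270, one-sided α = 0.025 (section 5.7, Table 3); looks at 175 and 270, efficacy bound 2.5469, futility bound 0.9365, final bound 1.9896 (Table 4).

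With information I = N/(4·SD²), the final statistic has mean δ√I and the interim statistic has mean δ√(I·175/270). Rejection probability is P(Z₁ > 2.5469) + P(0.9365 < Z₁ < 2.5469, Z₂ > 1.9896).
- δ = 0.9: 80.0% overall, 40.9% at the interim (stated: 80.05% and 40.95%).
- δ = 0: 2.35% overall, 82.5% futility stops (stated: 2.36% and 82.5%).

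The plan's figures reproduce.

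**Step 4: add an assumed bias.** If withdrawn subjects in both arms have the same gap between imputed and true mean change,

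bias = (withdrawal rate on riluzole − rate on placebo) × (imputed − true mean change).

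The protocol gives neither factor, so both are assumptions. Equal rates with an equal gap give zero bias.

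| Assumed rate difference | Assumed gap (points) | Bias (points) | Type I error if toward riluzole | Power if against riluzole |
|---|---|---|---|---|
| none | any | 0 | 2.35% | 80.0% |
| 1.4 percentage points | 1 | 0.014 | 2.6% | 78.8% |
| 1.4 percentage points | 2 | 0.028 | 2.9% | 77.5% |
| 5 percentage points (10% vs 5%) | 1 | 0.05 | 3.4% | 75.4% |
| 5 percentage points (10% vs 5%) | 2 | 0.10 | 4.7% | 70.2% |

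The 1.4-point row uses the Huntington's disease study described in section 3.2: five subjects stopped for raised liver enzymes, and 5/357 = 1.4% if all five are assumed to have been on riluzole and none on placebo. SD, N and bounds are held fixed throughout.

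**Step 5: room in the sample size.** 300 × 0.90 = 270, so the 10% allowance in section 5.7 exactly holds 80.0% power. At 15% total loss (255 left) power is 77.7%; at 20% (240 left) it is 75.2%. These are losses from all causes, not from this clause alone.

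**The case against.** The strongest reply is that 4.5.4.5 is the specific rule for missed capsules, while 4.6.3 only lists possible reasons for withdrawal and sets no compliance threshold that triggers it. Other text fits retention: the duty to try to keep subjects, an ITT population defined whatever treatment was received, and a separate per-protocol set at 80% of medication. A one-line cross-reference would settle it. This has force: the conflict is easy to repair and 4.6.3 does not compel withdrawal. But the protocol nowhere says that the specific rule prevails, so the conflict stands.

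Two stronger readings are tempting and are not supported. A reader might infer that safety withdrawals also contradict 4.5.4.5. They do not, because that section covers medication compliance only. A reader might also infer that anyone who stops riluzole for a side effect automatically loses the 180-day visit. No section equates stopping study drug with leaving the study; withdrawal under 4.6.3 needs a separate act by the investigator, and a subject who merely falls below 80% comes under the retention sentence.

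On size, a 10% versus 5% split puts the whole 10% allowance, which section 5.7 also assigns to baseline adjustment, on one clause in one arm. Section 3.2 describes adverse effects as nearly alike between arms in the Huntington's disease study. The imputation method may be set in the separate analysis plan, and subjects withdrawn after the 35-day visit would have an mJOA that imputation could use. Some arm difference would also come from consent withdrawal and loss to follow-up, which the fix does not alter. All of this stands, and is why the figures are illustrative only.

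**Conclusion.** The point holds in limited form. There is a real contradiction for medication non-compliance. For investigator withdrawal generally, including on safety grounds, there is a gap: the protocol does not say whether the 180-day mJOA is still collected. The result is an avoidable risk that observable primary outcomes become imputed ones.

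That the trial will be biased, or biased in a known direction, does not follow. Bias needs withdrawal or the outcome gap to differ by arm, and it depends on an imputation method not shown here. Under the assumed inputs the effect runs from slight (type I error 2.6%–2.9%, or power 79%–77%) to material (3.4%–4.7%, or 75%–70%). No figure in the sample-size section is wrong. This should be fixed, but it does not invalidate the design.

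**What to change.** Reconcile sections 4.5.4.5 and 4.6.3 so that one rule governs subjects who are non-compliant with study medication, with a cross-reference between them. In 4.6.3, define *discontinued study drug* separately from *withdrawn from study*. State that subjects who stop study drug or are non-compliant with it, and who still consent, keep the scheduled outcome visits, at least the 180-day mJOA. Record drug discontinuation and study withdrawal as separate events, with reasons.

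This concerns outcome collection only. When a subject stops treatment remains the investigator's decision, and the safety-withdrawal provision need not be removed.

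The cost is about one paragraph of wording, site training, and continued visits, already in the schedule, for a few subjects.

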### 4.6.4 Lost to Follow-up

---

A subject will be considered lost to follow-up if they do not come for the scheduled study visit and the study personnel is unable to contact the subject. The study personnel must perform and document the following contact attempts prior to declaring a subject to be lost to follow-up: three phone calls with at least 2 days in between each call followed by a certified letter. The first phone call must occur latest 3 business days after subject has failed to show up for the visit.

### 4.6.5 Completed Subject

---

A subject will be considered as having completed the study if he/she has completed all assessments through the 365-day visit. Subjects who do not reach 365 days since the surgery at the time when the trial is stopped for enrollment will be considered as completed if they have completed all assessments through the 180-day visit. If the subject has reached 365 days since surgery before the end of study enrollment, but subject missed visit(s) due to being withdrawn, lost to follow-up, or deceased, he/she will not be categorized as having completed the study.

## 5 Statistical Analysis

---

Details of the statistical analysis will be included in the Statistical Analysis Plan (SAP), which will be provided as a separate document. This section provides key elements of the statistical approach.

### 5.1 Primary Efficacy Endpoint

---

The primary efficacy endpoint in this study is absolute difference in mJOA between 180 days follow-up and baseline.

$$\Delta mJOA_{180-b} = mJOA_{180 \text{ days}} - mJOA_{\text{baseline}} (1)$$

### 5.2 Secondary Efficacy Endpoints

---

1. Absolute change in Nurick score from admission to 180 days
2. Absolute change in SF-36v2.0™ PCS from admission to 180 days
3. Absolute change in Neck Disability Index (NDI) from admission to 180 days
4. Absolute change in Cervical Pain Numeric Rating Scale from admission to 180 days
5. Absolute change in EQ-5D utility score from admission to 180 days
6. Absolute change in ASIA Motor Score from admission to 180 days
7. Absolute change in ASIA Sensory Score from admission to 180 days
8. Absolute change in Grip Strength from baseline to 180 days
9. Rate of neurological complications

### 5.3 Other Endpoints

---

1. Absolute change in mJOA score from admission to 35 days, and 365 days
2. Absolute change in Nurick score from admission to 35 days, and 365 days
3. Absolute change in SF-36v2.0™ PCS score from admission to 35 days, and 365 days
4. Absolute change in NDI score from admission to 35 days, and 365 days
5. Absolute change in SF-36v2.0™ MCS score from baseline to 35 days, and 365 days
6. Absolute change in SF-36v2.0™ eight dimensions from baseline to 35 days, and 365 days
7. Absolute change in EQ-5D from baseline to 35 days, and 365 days
8. Absolute change in ASIA Motor Score from baseline to 35 days, and 365 days
9. Absolute change in ASIA Sensory Score from baseline to 35 days and 365 days
10. Absolute change in Grip Strength from baseline to 35 days, and 365 days
11. Absolute change in Cervical Pain NRS from admission to 35 days, and 365 days
12. Absolute change in Bazaz from admission to 35 days, 180 days, and 365 days
13. Systemic (non-neurological) complications
14. Changes in all outcome parameters (mJOA, Nurick, SF36v2, NDI, EQ-5D, ASIA Motor Score, ASIA Sensory Score, Grip Strength, Cervical Pain NRS, Bazaz) between -14 days and the pre-operative visit

15. Changes in outcome parameters over follow-up time (-14, pre-operative, 35, 180 and 365 days).

### 5.3.1 Complications and AE

---

Complications and AE will be recorded according to descriptions provided in Section 6.

## 5.4 Study success

---

### 5.4.1 Main Definition of Success

---

The study success is defined as follows:

Investigational treatment (riluzole) is superior to placebo. The study success is achieved if one-sided null hypothesis of no superiority of riluzole group in  $\Delta mJOA_{180-b}$  is rejected.

### 5.4.2 Alternative Definition of Success

---

The alternative definition of success is if ANY of the following secondary efficacy hypotheses has been rejected.

1. One-sided null hypothesis of no superiority of riluzole in change in ASIA Motor Score between the baseline and the 6 months post-surgery.
2. One-sided null hypothesis of no superiority of riluzole in change in Nurick score between the baseline and the 6 months post-surgery.
3. One-sided null hypothesis of no superiority of riluzole in change in NDI score between the baseline and the 6 months post-surgery.

## 5.5 Statistical Testing of Primary Endpoint (mJOA)

---

The appropriate statistical approach is to test a single one-sided null-hypothesis that the difference between the Investigational and the Placebo arm is equal to or less than 0. Rejection of null-hypothesis is consistent with superiority of investigational treatment.

$$H_0: \mu_i - \mu_c \leq 0$$

$$H_1: \mu_i - \mu_c > 0$$

Where:

$\mu_i$  and  $\mu_c$  are the means of the two independent normal distributions;

$\mu_i$  is the mean population value of the  $\Delta mJOA_{180-b}$  in the patients treated with riluzole;

$\mu_c$  is the mean population value of the  $\Delta mJOA_{180-b}$  in the patients treated with placebo.

The hypothesis will be tested by one-sided t-test at the alpha level of 0.025. If the test value exceeds the nominal critical point, the  $H_0$  will be rejected.

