#### 4.1.1 Primary Endpoint

---

- Absolute change in mJOA from admission to 180 days

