### 4.5.2.3 Visit 2: Enrollment (15-21 days prior to surgery)

---

This visit occurs 15-21 days before the surgery and prior to the first dose of study medication. This visit can be performed on the same day as the screening visit or on two separate days. If performed on two separate days, the Investigator and the Study Coordinator should ensure that:

- The screening data are current

---

 Visit 1 and Visit 2 can be combined into one physical visit

Efficacy of Riluzole in Patients with Cervical Spondylotic Myelopathy Undergoing Surgical Treatment. A Randomized, Double-Blind, Placebo-Controlled, Multi-Center Study

- The patient's screening mJOA test was performed in less than 21 days prior to surgery. If not, repeat the mJOA.
- The patient's clinical manifestation has not significantly worsened (investigator's opinion) since the Visit 1. If yes, repeat the mJOA.

If the patient fails inclusion/exclusion criteria, the patient should not be enrolled to the study by the Investigator and the subject will be handled as a screen failure, the reason for the screen failure will be recorded on the screening source worksheet, data shall be entered into eCRF within 14 calendar days of data collection.

The following procedures are performed during the visit:

- Obtain socio-economic, health behavior, medical history, vitals, and information about concomitant medications
- Investigator:
  - Perform and record mJOA, Nurick Score, Grip Strength and complete ASIA examination
- Subject completes questionnaires:
  - NDI, Pain NRS, SF-36v2™, EQ-5D, Bazaz
- Review and verify all data collected to confirm the subject meets all study inclusion/exclusion criteria.
- **Enroll subject**
- Perform randomization procedure and enter randomization code into the Randomization Log
- Update information in the Screening Form
- Provide subject with *Bottle#1* of study medication and record on the Study Medication Dispensing CRF
- Provide subject with a Medication Compliance Diary to fill out the information about the treatment dates and times
- Teach subject how to take the medication and fill out the Medication Compliance Diary
- Inform subject to bring the Medication Compliance Diary and any unused medication with its container to the next visit (admission)
- Log the subject's drug accountability information into the Site Drug Accountability Log
- Advise subject not to take medications in the exclusion list
- Check source worksheets for completeness

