## 5.7 Sample Size Estimate

---

The required sample size is 270 evaluable subjects, or 135 subjects per study arm. The rationale for the sample size is as follows.

Sample size has been calculated to provide 80% power in testing the primary superiority hypothesis. The estimate has been made by the sample size estimation software package East v5.3 (Cytel, Inc.).

Using the data from the performed CSM study (data on file with the Sponsor), the following empirical estimates have been obtained for the primary outcome parameters.

| Endpoint              | N   | Mean | Standard Deviation |
|-----------------------|-----|------|--------------------|
| $\Delta mJOA_{180-b}$ | 146 | 2.81 | 2.57               |

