**Table 3 Sample size estimate  $\Delta mJOA_{180-b}$**

| Plan ID                                           | Parameter          |
|---------------------------------------------------|--------------------|
| Type of the hypothesis                            | 1-Sided            |
| Type I Error ( $\alpha$ )                         | 0.025              |
| Power ( $1 - \beta$ )                             | 0.80               |
| Randomization Ratio (Investigational vs. Control) | 1:1                |
| Planned Number of Interim Looks                   | 2                  |
| Spacing of Looks                                  | 65%, 100%          |
| Hypothesis to be Rejected                         | H0 or H1 (binding) |
| Boundary Family                                   | Published Function |
| Boundary to Reject H0                             | O'Brien-Fleming    |
| Boundary to Reject H1                             | Gamma (-2)         |
| Difference of Means Assuming $H_1$                | 0.9                |
| Standard Deviation ( $\sigma$ )                   | 2.57               |
| Sample Size                                       | 270 (135 per arm)  |

Under the above assumptions, the estimated sample size is 270 evaluable subjects. (135 in the riluzole arm and 135 in the control arm). In order to account for loss of power due to loss of follow-up and possible adjustments for baseline factors we will increase sample size for 10% to **300 enrolled** subjects.

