**Table 5. Simulation results: difference between investigational and control group is 0.9 absolute points in mJOA**

[figure not shown]

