## 5.11 Randomization

---

The randomization will be performed at 1:1 ratio between the investigational and the control arm. Sequenced and sealed envelopes or a similar randomization approach will be given to participating centers. Randomization will be carried out according to the blocks procedure. Block randomization is used to assign eligible patients to the treatment arms in order to avoid serious imbalance in the number of participants assigned to each group within a center. The pattern of the blocks will be concealed to avoid selection bias. Two block sizes will be used, with 2 and 4 subjects per block. Block sizes will be chosen at random. The order of block sizes will be randomly shuffled. This scheme makes breaking the blinding by working out the block pattern extremely difficult and reasonably protects against biased allocation of patients.

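### The primary test is an unadjusted t-test on the change in mJOA; it is valid, but it forgoes precision available from pre-dose mJOA and centre

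*Protocol*

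**What the plan says.** Section 5.1 defines the endpoint: "The primary efficacy endpoint in this study is absolute difference in mJOA between 180 days follow-up and baseline". Section 4.1.1 makes the starting point explicit: "Absolute change in mJOA from admission to 180 days". Section 5.5 compares the mean change in two independent normal populations, with no covariate and no stratum term: "The hypothesis will be tested by one-sided t-test at the alpha level of 0.025".

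Section 5.11 blocks the randomisation, in sizes 2 and 4, "in order to avoid serious imbalance in the number of participants assigned to each group within a center". Section 3.3 allows up to 16 sites.

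The protocol also collects an mJOA before any study drug is taken. At the enrolment visit (Section 4.5.2.3) the investigator is to "Perform and record mJOA, Nurick Score, Grip Strength and complete ASIA examination". Table 1 also places an mJOA at screening.

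On power, Section 5.7 says "Sample size has been calculated to provide 80% power in testing the primary superiority hypothesis", using the SD of the raw change score, 2.57. The only mention of adjustment comes after Table 3. There, loss of power is linked to loss of follow-up and to "possible adjustments for baseline factors we will increase sample size for 10" per cent, giving 300 enrolled. No covariate is named and the test in Section 5.5 is unchanged.

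**The concern.** Subjects enter with a screening mJOA anywhere from 8 to 14, so the room to improve differs between them. A change score assumes that each extra baseline point carries through to one extra point at 180 days. If the true slope is below 1, the change score over-corrects: when one arm happens to start d points higher, its mean change is pulled down by (1 − slope) × d. The same mismatch inflates the residual variance. An analysis that estimates the dependence on baseline avoids both.

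Centre is similar. Blocking balances the arms within centre. If centres differ in outcome, the t-test still counts those differences as noise, so its standard error is too large and the test is conservative.

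At stake is power in a trial planned at 80%, and the exposure of both looks to chance imbalance. In addition, Section 5.7, read naturally, treats baseline adjustment as something that consumes power. That rationale could discourage the better analysis.

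**Working it through.** **Inputs from the protocol.** Difference 0.9, SD of change 2.57, one-sided alpha 0.025, power 80%, 1:1 allocation, looks at 65% and 100% (Section 5.7, Table 3). Bounds on the z scale: efficacy 2.5469 and futility 0.9365 at the first look, 1.9896 at the final (Table 4). Up to 16 sites (Section 3.3).

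**Inputs assumed, because the protocol does not give them.** Correlation |r| between the change and the baseline covariate, 0 to 0.5. Between-centre share of variance (ICC), 0.01 to 0.10.

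**1. Reproduce the stated size.** In a fixed design, n per arm = 2 × (1.960 + 0.842)² × 2.57² / 0.9² ≈ 128, or 129 with the t distribution (258 in total). With two looks, the drift at 270 is 0.9 / (2.57 × √(4/270)) = 0.9 / 0.3128 = 2.877, and at the first look 2.877 × √0.65 = 2.320.
- Chance of crossing 2.5469 at the first look: 1 − Φ(0.227) = 41.0%.
- Adding the paths that lie between the two first-look bounds and then exceed 1.9896: 80.05%.
- Size for 80% power: 269.6, against 270 stated.

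So 270 is correct for the unadjusted test. The text of Section 5.8 calls the effect 1 point, but its 40.95% and 80.05% belong to the 0.9 in the Table 5 title ("difference between investigational and control group is 0.9 absolute points in mJOA"). A true difference of 1 would give 51.2% and 87.6%.

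**2. Adjust for baseline.** Residual SD = 2.57 × √(1 − r²), and the size for 80% power scales by (1 − r²). For |r| = 0.3: 2.57 × √0.91 = 2.45 and 269.6 × 0.91 = 245.

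| assumed \|r\| | residual SD | N for 80% | power at 270 |
|---|---|---|---|
| 0 | 2.57 | 270 | 80.05% |
| 0.1 | 2.56 | 267 | 80.5% |
| 0.2 | 2.52 | 259 | 81.6% |
| 0.3 | 2.45 | 245 | 83.6% |
| 0.4 | 2.36 | 227 | 86.4% |
| 0.5 | 2.23 | 202 | 89.9% |

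**3. Add centre.** Residual SD = 2.57 × √(1 − ICC).

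| assumed ICC | N for 80% | power at 270 |
|---|---|---|
| 0.01 | 267 | 80.5% |
| 0.05 | 256 | 82.0% |
| 0.10 | 243 | 84.0% |

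That is a gain of about 0.4 to 4 points. Both together, with |r| 0.3 and ICC 0.05, give N 233 and power 85.5%.

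**4. Cost in degrees of freedom.** The t-test has 270 − 2 = 268. One baseline slope and at most 15 centre terms use 16, leaving 252.

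**5. Illustration of over-correction.** Assume a baseline SD of 2.0 (an even spread over 8 to 14) and a slope of 0.5. One standard error of chance imbalance at the first look, with 175 subjects, is 2.0 × √(4/175) = 0.30 points. It shifts the difference in change by 0.5 × 0.30 = 0.15. Section 5.8 puts the futility stop at about 0.35.

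**6. The increase to 300.** 270 / 0.90 = 300, so a 10% loss of follow-up accounts for all of it and leaves nothing for adjustment.

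**The case against.** The strongest reply is that nothing here is wrong. The two-sample t-test is valid under randomisation, leaving out a blocking factor errs on the conservative side, and test, SD and sample size agree with one another. All of that stands.

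A reader might infer three stronger claims that the documents do not support.
- *That the test ignores baseline, or leaves chance imbalance uncorrected.* It does not. Section 5.1 subtracts baseline. The fault is the fixed slope of 1, which over-corrects if the true slope is smaller.
- *That the trial is underpowered, or that 270 should be cut.* The stated size reproduces. The smaller sizes above rest on an assumed correlation, and the range includes no gain at all.
- *That 180-day mJOA and change from admission can be swapped freely in an ANCOVA.* They give the same treatment estimate only if the covariate is the baseline that was subtracted. Admission follows about 14 days of study drug. With a pre-dose covariate, 180-day mJOA would include any preoperative drug effect and change from admission would exclude it.

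It can also be said that Section 5 leaves details to the SAP and that Section 5.7 foresees adjustment. But Section 5.5 names the primary test outright. The sentence in Section 5.7 can be parsed as allowing for two separate things, lost power from dropout and possible adjustments. Its natural reading makes adjustment a cause of lost power, and on either reading adjustment is offered as a reason to enrol more subjects.

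**Conclusion.** The point holds as an efficiency weakness that can be removed at almost no cost. The primary test forgoes precision that data already collected, and the blocking already used, could supply. The gain cannot be read from the documents. Under the assumed |r| of 0 to 0.5, power at 270 lies between 80% and about 90%; below about 0.2 the benefit is under two points. Centre adds about 0.4 to 4 points for ICC 0.01 to 0.10. These figures also assume that 2.57, taken from the sponsor's earlier study, applies to this population.

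The rationale in Section 5.7 is wrong on its natural reading whatever the correlation: in a linear model, adjusting for a prognostic pre-treatment factor costs degrees of freedom and otherwise does not reduce power.

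**What to change.** Keep the endpoint as stated, change in mJOA from admission to 180 days. In Section 5.5, make the primary test an ANCOVA of that change on treatment, with two covariates:
- the last mJOA before the first dose, meaning the enrolment value, or the screening value where it was not repeated. The admission value should not be the covariate, because it is measured after randomisation and on study drug;
- centre, with small centres pooled by a rule set in advance.

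Test one-sided at the existing group-sequential bounds and keep the t-test as a sensitivity analysis. The SD reviewed for sample size under Section 5.9 should then be the residual SD of this model. In Section 5.7, attribute the 10% increase to loss of follow-up only.

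The cost is protocol and SAP wording, settled before any unblinded look, and at most about 16 of 268 degrees of freedom. No new data and no change in sample size are needed.
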